
#### EMDR therapy

Only parents who report clinical PTSD symptoms assessed with the PTSD Checklist for the DSM-5 (PCL-5, score ≥31 [60]) during post-test 1 (see Fig. 2) are randomized to one of the trauma therapy conditions (EMDR versus waitlist usual care). For a more detailed explanation of this instrument and the cut-off score that was used, see the “Outcomes {12}” section. EMDR therapy is a protocolized, eight-phase trauma therapy, which aims to reduce symptoms resulting from disturbing and unprocessed traumatic experiences. This method includes history taking, preparation, assessment, desensitization, installation, body scan, positive closure, and reevaluation [61]. Before the onset of the EMDR sessions, a case conceptualization is made with the parent (1 session of max 90 min) to identify the traumatic events that are currently related to their PTSD symptoms and have the most negative impact on the parent-child relationship. These may be traumatic experiences during and before parenthood, for example during childhood. Memories will be placed in a hierarchy based on the Subjective Units of Disturbance (SUD) and are treated subsequently from high to low SUD. During treatment, patients are asked to memorize the most distressing part of the experienced traumatic event, including images, thoughts, emotions, and physical sensations. At the same time, their working memory capacities are challenged by visually tracking the horizontally moving finger of the therapist (or a light bar) or other stimuli to maximize the workload of the working memory, such as hand-held buzzers. For a full description of the treatment protocol, see Shapiro [61]. In the current trial, the Dutch version of the standard EMDR protocol is used [62] and a maximum of 5 weekly sessions of EMDR therapy will be applied with a duration of 90 min each. It is assumed that some of the participants are able to process multiple memories per session. Therefore, early completers are expected in this study. Treatment completion is defined as receiving five sessions, or less if (a) SUD scores are zero for all identified traumatic memories and (b) there is an agreement between the parent and therapist that the PTSD symptoms are sufficiently reduced to warrant terminating treatment.

### Criteria for discontinuing or modifying allocated interventions {11b}

In case a mother refuses NIKA or EMDR, or does not want to complete all treatment sessions, we still aim to complete the research assessments for the dyad.

### Strategies to improve adherence to interventions {11c}

We apply several strategies to optimize treatment adherence in this trial. All NIKA therapists have a university-level degree. Training for NIKA involves a 3-day course, followed by a supervision trajectory and e-learning modules. For EMDR, trial therapists are licensed clinical psychologists who completed an EMDREA (EMDR Europe Association)-accredited EMDR training (basic and advanced level).

During this trial, all therapists will attend monthly supervision groups of 1 h for both NIKA and EMDR. One of the NIKA developers (KZ or ND) and an EMDREA-approved consultant ([name]) will review videotapes of NIKA and EMDR sessions. KZ and [name] will also review all case conceptualizations and session checklists for NIKA and EMDR, respectively. Additional supervision will be provided via email and telephone upon request. Finally, 10% of the videotapes of treatment sessions will be randomly selected, stratified on therapist and session, and rated for adherence, by trained Master students who are blinded to outcome and trained to assess adherence using NIKA- and EMDR-specific fidelity checklists.

### Relevant concomitant care permitted or prohibited during the trial {11d}

Participating dyads do not receive parent-child interventions (aside from some general forms of parenting support, such as psycho-education) or specialized trauma therapy during the 13 weeks of their participation in the study other than NIKA and EMDR therapy if they are allocated to these interventions.

### Provisions for post-trial care {30}

Not applicable, post-trial care will not be necessary for the participating dyads because they receive care from the domestic violence shelter throughout and directly after participating in this study. Dyads who were allocated to the waitlist usual care group will receive NIKA and EMDR directly after participating in this study.

### Outcomes {12}

The main parameters of this study are disrupted parenting behavior, sensitive parenting behavior, and PTSD symptoms of the mother. Disrupted parenting and sensitive parenting behavior are measured based on a 10-min mother-child observation, with the Atypical Maternal Behavior Instrument for Assessment and Classification (AMBIANCE) [63] and Ainsworth Sensitivity Scale [64], respectively. These observational instruments were chosen for this study for several reasons. First, these observational scales are both rooted in attachment theory and fit well with the goals of NIKA, during which the mothers receive explicit feedback on both disrupted and sensitive parenting behaviors. Second, by using observational instruments rather than self-reported parenting behavior, we obtain a less biased view of the quality of parenting behavior. Finally, both measures have good psychometric properties and are commonly used in our field. In the analyses, we will compare changes in parenting behavior from the pre-test to the first post-test between the two conditions (NIKA versus waitlist usual care), see the “Sample size {14}” section for more details about the analyses.

Maternal PTSD symptoms are measured with a self-report questionnaire, the PCL-5 and Life Events Checklist for the DSM-5 (LEC-5) [60]. We chose this instrument, because this is a widely accepted self-report measure of PTSD symptoms [65] and this version is consistent with the most recent version of the DSM (DSM-5). International validation studies have shown excellent psychometric properties of this questionnaire [66, 67]. Recently, a preliminary validation study also demonstrated good reliability and validity in the Netherlands [68]. Because of practical reasons (i.e., time to conduct a more elaborate measure and burden of the mothers during the research appointments), and because we are interested in the overall amount of distress mothers experience due to their previous traumatic experience, rather than whether or not they have an official diagnosis of PTSD, we decided not to use a more extensive measure of PTSD (such as the Clinician-Administered PTSD Scale for DSM-5 [69]). Because the PCL-5 had not yet been validated in a Dutch population at the time this study started, we relied on international validation studies to determine a cut-off score for clinical PTSD symptoms [66, 67]. These studies showed that cut-off scores between 31 and 33 are most predictive of PTSD. Because the goal of our study is to reduce clinically meaningful PTSD symptoms and related psychopathology in mothers, we decided to use the lower side of this range as a cut-off for clinical PTSD symptoms (score of 31). A sum score of the PCL-5 will be used in the analyses for each participant. We will compare changes in maternal PTSD symptoms from the first post-test to the second post-test between two conditions (EMDR versus waitlist usual care), see the “Sample size {14}” section for more details about the analyses.

The secondary outcomes of this study are PTSD symptoms and emotional and behavioral problems of the child. PTSD symptoms of the child are assessed with the Child and Adolescent Trauma Screen (CATS, version for 3–6 years [70]), which is filled out by the mother and involved social worker. This questionnaire is only used for children older than 12 months. We chose this measure because this measure is, to our knowledge, the only internationally validated screening questionnaire for PTSD symptoms in preschool children that is consistent with DSM-5. In addition, the same (practical) arguments as for our rationale to choose for the PCL-5, apply for our decision to work with the CATS rather than a more extensive measure of children’s PTSD symptoms (such as the Diagnostic Infant and Preschool Assessment [71]). The CATS has been validated for samples of children aged 3–6 years in the USA, Germany, and Norway [70]. The CATS has not yet been validated in a Dutch sample (a validation study is currently ongoing), nor for children younger than 3 years. We will compare changes in child PTSD symptoms (sum score, aggregated for the two informants) from the pre-test to the first post-test between two conditions (NIKA versus waitlist usual care), see the “Sample size {14}” section for more details about the analyses.

For the assessment of emotional and behavioral problems, the Child Behavior Checklist (CBCL) 1.5–5 years [72] is filled out by the mother and the Teacher Report Form (TRF) 1.5–5 years [72] is filled out by the involved social worker or another professional who is involved with the child, such as a caregiver from a child care center. Similar to the CATS, these questionnaires are only used for children older than 12 months. We chose these Achenbach System of Empirically Based Assessment (ASEBA) forms because they are widely used throughout the world and have well-documented psychometric properties. We will compare changes in emotional and behavioral problems (sum score, aggregated for the two informants) from the pre-test to the first post-test between two conditions (NIKA versus waitlist usual care), see the “Sample size {14}” section for more details about the analyses.

Furthermore, several background variables are assessed in this study: demographic variables (e.g., age, gender, SES), parental psychopathology (assessed at all time points with the Brief Symptom Inventory (BSI)-18 [73]), the maltreatment history of the child (assessed with the Modified Maltreatment Classification System [MMCS] based on case file coding [74]), parental childhood trauma (assessed during pre-test with the Childhood Trauma Questionnaire Short Form; CTQ-SF; [75]), and received professional support (e.g., other types of therapy provided to the family during the study, assessed based on case file coding). In addition, we will document all relevant characteristics of the participating domestic violence shelters (e.g., type of care that is provided to the families) and therapists (e.g., work experience, treatment fidelity).

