The estimated effect size of EMDR therapy on PTSD symptoms of the mother is based on a recent meta-analysis in which effect sizes of EMDR therapy were reported within a range of *g* = 0.67–1.18 [79]. Because the current implementation of EMDR therapy (focus on memories of traumatic events that are related to their PTSD symptoms and also hinder positive parent-child interactions) is different from previous studies, we decided to stay on the conservative side of this range by assuming an effect size of *d* = 0.60 for this study. We estimated three-level models accounting for repeated measures over time (level 1) and nesting of mothers (level 2) within the previous condition (NIKA versus waitlist) (level 3). We estimated approximately 50% variance to occur between subjects and 5% variance between previous conditions (NIKA versus waitlist). For a sample of *N* = 80, (*n* = 40 per group), two time points, and two-sided testing with a significance level of *α* = .05, we will have 75% power to detect effects of *d* = 0.60. With a sample of *N* = 150 in phase 1, this would imply that 53% of the mothers who are recruited for this study should report clinical trauma symptoms in order to be included in the randomization for phase 2. We made this estimation based on a recent report which revealed that all women in one of the participating domestic violence shelter locations experienced severe and chronic domestic violence and 75% of the women report traumas of their own childhood [80].

To explore the synergetic effect of NIKA and EMDR therapy, a two-level analysis (only accounting for repeated measures over time, thus not considering nesting of families within therapists), estimating 80% variance to occur between subjects, we will have 68% power to detect effects of *d* = 0.50.

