## Data collection and management

### Plans for assessment and collection of outcomes {18a}

At all three time points, the mother-child dyad is invited for a 1-h research appointment. All research appointments are similar in structure and content. After a short explanation of the (assistant-)researcher, the mother is asked to fill out a general questionnaire (only during the pre-test), the BSI [73], and CATS [70]. Then, a 10-min free play observation is conducted and videotaped. During the first 5 min of this observation, the mother and child are instructed to play together without toys as they would normally do. Next, a set of toys is provided, and the mother and child are instructed to play with these toys as they would normally do. The set of toys consists of a too large variety of toys, including a hand puppet, a toy that can make much noise, and age-inappropriate toys. Also, ambiguous toys (such as a spider and a police car) are included. After 4 min, the mother is instructed to clean up the toys with her child. These elements were included to make the play session a bit more challenging and stressful for the mothers. After the observation task, the mother is asked to fill out the CTQ [75], LEC-5 [60], PCL-5 [60], and CBCL [72]. All questionnaires are filled out on a laptop using the survey platform Qualtrics, or, in case this has the mother’s preference, on paper. The researcher remains in the same room during the administration of the questionnaires, so that the mother can ask questions. Because some questionnaires may elicit negative emotions in the mothers, the researcher remains vigilant of any signs of distress in the mother while she is filling out the questionnaires. If this occurs, the researcher will comfort the mother and pause the research appointment as long as necessary. At the end of the research appointment, the researcher will point the mother towards the possibility to contact her social worker if she would like to talk about anything related to the questionnaires. Even though the child is present during the observation talk, whenever possible the child will not be in the same room while the mother fills out the questionnaires. In most domestic violence shelters, there is an internal child care facility where the child can stay during this time. If this is not an option, the second researcher who is present will watch the child in another room while the mother fills out the questionnaires.

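### The phase 2 primary PCL-5 test is fixed as a change between the two post-tests, and the pre-test PCL-5 scheduled before the second randomisation has no stated use: a modest, avoidable loss of precision

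*Protocol article*

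**What the plan says.** The EMDR hypothesis on maternal PTSD symptoms is one of the primary hypotheses (Objectives {7}). Outcomes {12} fixes its comparison: "We will compare changes in maternal PTSD symptoms from the first post-test to the second post-test between two conditions (EMDR versus waitlist usual care".

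Sample size {14}, Phase 2, is written for the same design: n = "40 per group), two time points, and two-sided testing with a significance level of" .05. The variance assumption is "We estimated approximately 50% variance to occur between subjects and 5% variance between previous conditions (NIKA versus waitlist", and the result is that "we will have 75% power to detect effects of *d* = 0.60". Statistical methods {20a} names a three-level mixed model and refers back to these two sections for detail.

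Plans for assessment and collection of outcomes {18a} describes the research appointments at all three time points and lists the PCL-5 among the questionnaires. It says: "All research appointments are similar in structure and content". Participant timeline {13} likewise describes the first post-test as similar to the pre-test. Sequence generation {16a} places the EMDR randomisation after post-test 1. A PCL-5 is therefore scheduled about six weeks before the phase 2 baseline, ahead of EMDR allocation.

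No section gives that score a role. The phase 1 comparisons and the NIKA-plus-EMDR comparison in {20b} concern parenting and child outcomes only.

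**The concern.** A measurement of the same outcome taken before randomisation is a legitimate prognostic covariate. It cannot bias the randomised contrast, and it can narrow the confidence interval without new data.

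The saving matters here because this is the weakest of the primary tests: 75% power, against 86% for phase 1. The 80 mothers also depend on 53% of the 150 reaching the PCL-5 cut-off at post-test 1, and the power calculation states no allowance for dropout. A two-time-point change score sets aside the pre-test score altogether. It also gives the post-test 1 score a fixed weight of one instead of letting the data set the weight.

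**Working it through.** **Inputs from Sample size {14}, Phase 2:** n = 40 per group, d = 0.60, two-sided α = .05, two time points, about 50% of variance between subjects. Taken as a random-intercept structure with unit variance, 50% means that any two PCL-5 scores on the same mother correlate at ρ = 0.50.

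**Method.** Power from the noncentral t, with noncentrality d / √(v × 2/n), where v is the variance of the quantity compared between arms.

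**Step 1. Reproduce the stated figure.** For a change score v = 2(1 − ρ) = 2 × 0.50 = 1.00. The noncentrality is 0.60 / √(1.00 × 2/40) = 2.68, and power is 75.5% (stated: 75%). The same formula with n = 75 and d = 0.50 gives 86.0% for phase 1 (stated: 86%). The published figures therefore behave as two-time-point change-score tests.

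**Step 2. Post-test 1 as covariate.** v = 1 − ρ² = 1 − 0.25 = 0.75. Noncentrality 3.10, power 86.4%.

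**Step 3. Post-test 1 and pre-test as covariates.** With all correlations equal, v = 1 − 2ρ²/(1 + ρ) = 1 − 0.50/1.50 = 0.667. Noncentrality 3.29, power about 90%. One further degree of freedom for NIKA condition does not change this.

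**Step 4. Divide the gain.** From 75.5% to 86.4% is about 11 points, due to covariate adjustment on post-test 1. From 86.4% to about 90% is about 4 points, due to the pre-test. The pre-test's share corresponds to an 11% lower residual variance (0.667/0.75 = 0.889).

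**Step 5. Vary the pre-test to week-13 correlation.** The protocol gives no value, so r is assumed. The two adjacent correlations are kept at 0.50, and v = 1 − (0.25 + r² − 0.50r)/0.75.

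| Assumed r | v | Variance reduction beyond Step 2 | Power |
|---|---|---|---|
| 0.25 | 0.750 | 0% | 86.4% |
| 0.30 | 0.747 | 0.4% | 86.6% |
| 0.35 | 0.737 | 1.8% | 87.0% |
| 0.40 | 0.720 | 4.0% | 87.7% |
| 0.45 | 0.697 | 7.1% | 88.8% |
| 0.50 | 0.667 | 11.1% | 90% |

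The value 0.25 is what first-order decay at 0.50 per six weeks would produce (0.50 × 0.50). In that case the pre-test adds nothing.

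**Step 6. Selection at the cut-off.** Only mothers scoring at least 31 at post-test 1 are randomised. A simulation with ρ = 0.50 that keeps the top 53% on post-test 1 gives variances of 0.846 (change score), 0.75 (post-test 1 as covariate) and 0.667 (both). The corresponding powers are 82%, 86% and 90%. Selection thus narrows the gap between the change score and covariate adjustment, and leaves the pre-test's own increment as it was. Adding the pre-test to a change-score model, without freeing the coefficient of post-test 1, moves power only from 82% to 83%. Without selection and with equal correlations it gains nothing, because the pre-test is then uncorrelated with the change.

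**The case against.** The strongest reply is that nothing here is an error. The change from post-test 1 to post-test 2 spans the period in which EMDR is given, the power calculation matches it, and covariate lists and imputation-model contents are commonly left to an analysis plan. That stands in part: the article does not exclude covariates, and the absence of a list would not be a finding. But the article does more than stay silent. It names the two time points, defines the contrast as a change between them, and powers it that way. The point is that a better use of scheduled data is available than the method stated.

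Four stronger readings do not hold:

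- **That the pre-test is worth 15 points of power.** Most of that gain belongs to a different change, covariate adjustment on post-test 1. The pre-test's share is the small part, and equal correlation over 6 and 12 weeks is the favourable end. Decay is plausible, since about half of the mothers are allocated to NIKA between the pre-test and post-test 1.
- **That the entry cut-off makes the pre-test especially valuable.** Truncation does weaken the correlation of post-test 1 with week 13, but the increment from the pre-test is 11% with or without selection.
- **That a pre-test score is in hand for every mother.** The article gives a schedule, not a guarantee. Some scores may be missing and would need imputation.
- **That the planned imputation is deficient.** Section {20c} says only that multilevel multiple imputation will be used. Nothing shows that the earlier PCL-5 would be left out.

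**Conclusion.** The point holds as a modest efficiency improvement. The phase 2 primary comparison, as stated, leaves a scheduled pre-randomisation PCL-5 unused. At the plan's own variance assumption, power is about 75% for the change score, 86% with post-test 1 as covariate and 90% with both earlier scores. The pre-test alone accounts for between 0 and about 4 of those points over an assumed pre-test to week-13 correlation of 0.25 to 0.50.

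These figures rest on 40 mothers per group with complete data, d = 0.60 on a unit-variance scale, a correlation of 0.50 between adjacent assessments, and no selection effect. With selection at the cut-off, the total gain is nearer 8 points (82% to 90%). A reader might infer that the planned test is biased or that the 75% is miscalculated. Neither follows: the change comparison is valid under randomisation, and the 75% reproduces.

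**What to change.** In Outcomes {12} and Statistical methods {20a}, state that in mothers randomised in phase 2, post-test 2 PCL-5 is modelled on EMDR arm with post-test 1 PCL-5, pre-test PCL-5 and NIKA condition as covariates. NIKA condition belongs in the model because NIKA is delivered between the two PCL-5 covariates, and the phase 2 power model already accounts for previous condition. An alternative is to fit all three time points with the two pre-randomisation means held equal across the EMDR arms. Both earlier scores must enter with free coefficients; adding the pre-test to a change-score model would gain almost nothing. State also that pre-test PCL-5 is in the imputation model.

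The sample-size statement need not change: 75% can be described as conservative. The cost is a sentence or two, one degree of freedom beyond adjustment for post-test 1, and imputation of any missing pre-test scores. No new data are needed. The change should be recorded before outcome data by EMDR arm are examined, so that it cannot be read as a choice made on the results.

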## Interventions

### Explanation for the choice of comparators {6b}

All dyads receive care as usual (CAU) in the domestic violence shelter. The comparison group in this study is placed on a waitlist for NIKA and, if applicable, EMDR. The main reason for this choice is that it would be unethical to withhold the participating dyads completely from these interventions. In addition, the domestic violence shelter already offers an environment in which families receive support to deal with the consequences of domestic violence. Mothers and their children usually reside in the domestic violence shelter for a period of 6 weeks to 9 months, depending on the domestic violence shelter organization and the possibilities for transitioning to permanent housing. After this period, further treatment is continued through ambulatory care. The goal of the guidance that is provided to women in the domestic violence shelter is to develop a safe environment and to learn how to become independent and how to prevent becoming involved in interparental violence again in the future. The standard guidance that is provided in the different domestic violence shelters is roughly similar: a social worker is involved with the family throughout their stay in the domestic violence shelter. This social worker also involves the social network, and, if possible, the non-residing parent in the treatment plan for the family. In addition, help is provided to mothers with respect to practical issues such as financial problems, schooling for the child and mother, legal issues, and future housing of the family. In addition to individual support, group activities (e.g., support groups for mothers) are regularly organized. Even though the participating domestic violence shelter organizations have slightly different emphases, both organizations use nationally available protocols for support in domestic violence shelters [56, 57]. Currently, these protocols do not include an assessment of the need to provide trauma- and attachment-based interventions nor routine offering of such intervention. If the mothers or children need more specialized support, this is provided by either an external youth care organization or by psychologists from the domestic violence shelter.

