NIKA is provided through a structured protocol. NIKA starts with an assessment session consisting of an attachment interview, a questionnaire, and a video observation. For the video observation, the parent and child are asked to play together for a couple of minutes while a few mild stressors are added. In this trial, the video recordings that are made during the pre-test are used for this purpose (stressors in this session include the use of age-inappropriate toys, a too large variety of toys, and the instruction to clean up the toys after a couple of minutes). The goal of the assessment is to get acquainted with the child’s attachment behaviors, the disrupted patterns that are present in the parent-child relationship, and the roots of these patterns in the parent’s own trauma history, as well as the parent’s reflective functioning and sensitive behaviors. After the assessment session, several video-feedback sessions take place. For this trial, we standardized the number of video-feedback sessions so that each dyad will receive four video-feedback sessions of 1 h each. These sessions have a similar structure: first, the therapist helps the parent formulate a personalized goal and reflect on the parent’s interactions with the child. The therapist and parent then discuss the video recordings that were made during the previous session. The therapist uses psycho-education (supported with visual materials) to explain what sensitive parenting behavior is and helps the parent reflect on his or her parenting behavior based on the psycho-education and video recordings. Throughout the session, the therapist stimulates the parent to mentalize about the child’s behaviors, thoughts, and feelings in the video recordings (e.g., “What is your child thinking right now?”). In case the parent has dysfunctional cognitions about the child (e.g., if the child is playing on its own and the parent interprets this behavior as if the child is rejecting him or her), cognitive restructuring techniques are used to change these cognitions. The parent is reinforced by the therapist whenever the parent displays adequate insights or reflections. To provide the parent with feedback on disrupted parenting behavior, the therapist selects a fragment that reflects a disrupted pattern in the parent-child relationship. The video is first paused at a moment where the child shows attachment-eliciting cues. The parent is asked what the child would feel, think, and need in this instant. Subsequently, the disrupted parenting behavior that follows in the video recording is displayed to the parent. The therapist reflects on this moment with the parent by discussing the relation between this parenting behavior and the parent’s own traumatic history. The parent is explained what the negative effect of this behavior is on his or her child, by showing the child’s response in the video recording and providing the parent with psycho-education. The therapist also gives the parent specific advice on how to improve the disrupted parenting behavior. At the end of the feedback session, the therapist shows a fragment in which the parent displays sensitive parenting behavior. This way, the parent is reinforced in his or her abilities as a parent and feels more confident. In the final session, the assessments of the intake session are repeated and the therapist and parent reflect on the effect of the feedback sessions.

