## Assignment of interventions: blinding

### Who will be blinded {17a}

Participating mothers and their therapists and social workers cannot be blinded for study condition in this trial, because the control group is placed on a waitlist. The research assessments only include self-report questionnaires (in the presence of a researcher) and a video observation with no interference from the researcher. Therefore, it is not necessary to blind the researchers who perform the assessments to the study condition of the dyad. All observational data in this study will be coded by researchers who are blind to the condition of the dyads.

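### Child outcomes are analysed only as a score pooled over the treated mother and a professional, so a shift in how the mother rates cannot be told apart from a change in the child

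*Protocol article*

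**What the plan says.** Outcomes {12} defines two secondary child outcomes, each as one score over two informants.

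- **Child PTSD symptoms.** The questionnaire is the CATS, "which is filled out by the mother and involved social worker". The analysis is: "We will compare changes in child PTSD symptoms (sum score, aggregated for the two informants) from the pre-test to the first post-test".
- **Emotional and behavioral problems.** The mother completes the CBCL. The TRF "is filled out by the involved social worker or another professional who is involved with the child". The analysis is: "We will compare changes in emotional and behavioral problems (sum score, aggregated for the two informants) from the pre-test to the first post-test".

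Both are compared between NIKA and waitlist usual care, and serve the secondary hypothesis in Objectives {7} that children of mothers given NIKA improve more.

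The NIKA part of the Intervention description {11a} says that "the therapist stimulates the parent to mentalize about the child’s behaviors, thoughts, and feelings in the video recordings". Where a mother holds dysfunctional beliefs about the child, "cognitive restructuring techniques are used to change these cognitions".

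On blinding, section {17a} states: "Participating mothers and their therapists and social workers cannot be blinded for study condition in this trial". Blinded coding applies to the observational data, and neither child outcome is observational.

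No informant-specific analysis appears in Outcomes {12}, Statistical methods {20a}, Additional analyses {20b} or the limitations set out in the Discussion.

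**The concern.** The mother is both the person treated and one of the two raters of the child. NIKA aims to change how she understands her child's behavior, which is also what she draws on when she fills in the CATS and CBCL. A mother who no longer takes solitary play as rejection may record fewer problems in a child who behaves as before. A mother who has become more alert to distress may record more.

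The hypothesis is about children's symptoms. If only the pooled score is analysed, a change confined to the mother's perception and a change in the child lead to the same reported result. In the opposite direction, a real benefit could be masked. The one rating not supplied by the treated person is already collected, but after aggregation nobody can see what it did. The aggregation is stated in the article itself, so this is a choice the document makes and not a detail it leaves open.

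**Working it through.** **Inputs from the protocol.** Sample size {14}: 75 per group in phase 1, two-sided alpha .05, d = 0.50 and 86% power for the parenting outcomes, about 50% of variance between subjects. No effect size or power is given for the child outcomes. The Discussion says children under 12 months are left out of these measures, without a count.

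**Inputs assumed.** The maternal rating shift b (0.3 to 0.5 SD, favouring NIKA), the mother-professional correlation r (0.2 to 0.4) and 68 children per arm are not in the documents. The professional's rating is set to show no effect.

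**Step 1: the plan's own figure, for context.** With a simple two-group formula, SE = √(2/75) = 0.163 and 0.50/0.163 = 3.06, which gives power of 86.5% (86.0% with the noncentral t). This agrees with the stated 86%, although it is not the three-level model that the protocol used.

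**Step 2: shift in the composite.** With 50% between-subject variance, the variance of a change score is 2 × (1 − 0.5) = 1, so its SD equals the raw SD. For the equally weighted mean of two standardised ratings:

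composite shift = (b/2) / √((1 + r)/2)

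- b = 0.3, r = 0.4: 0.15/0.837 = 0.18 SD
- b = 0.4, r = 0.3: 0.20/0.806 = 0.248 SD
- b = 0.5, r = 0.2: 0.25/0.775 = 0.32 SD

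The composite keeps about 60 to 65% of the maternal shift.

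**Step 3: chance of a significant result favouring NIKA.** At 68 per arm SE = √(2/68) = 0.171, and the probability is 1 − Φ(1.96 − shift/SE).

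- 0.18 SD: 18%
- 0.248 SD: 30%
- 0.32 SD: 47%

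With no shift the figure is 2.5%. For the same b and r it is about 16 to 42% at 60 per arm and 19 to 51% at 75 per arm.

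**Step 4: a mother-only score, same assumptions.** 1 − Φ(1.96 − b/0.171) gives about 42%, 65% and 83% at b = 0.3, 0.4 and 0.5. The composite is therefore less exposed than the mother's score alone.

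**Step 5: would it suffice that the professional's estimate points the same way?** The composite estimate and the professional's estimate have correlation √((1 + r)/2), which is 0.775 to 0.837 here. Among composites that are significant in favour of NIKA, the professional's estimate is also favourable in about 80 to 97% of cases (91% at b = 0.4, r = 0.3), because those composites reached significance partly through a chance favourable movement in the professional's score.

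**Step 6: how sharp is a direct comparison of informants?** The difference between the two informant effects has SE = 0.171 × √(2(1 − r)). At r = 0.3 this is 0.203, so b = 0.4 gives z of about 1.97 and power of about 50%. An informant-by-condition test is informative, but it cannot be the only safeguard.

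**The case against.** **Using two informants is itself a protection.** This stands. Step 4 shows that a mother-only score would be far more exposed. Pooling does not create the problem: it dilutes a maternal shift and hides it. Making the mother's score a separate confirmatory outcome would bring back the undiluted form and add tests.

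**The direction is not known.** This also stands. Cognitive restructuring is used only where dysfunctional cognitions are present, and greater awareness of the child's distress could raise symptom ratings. A reader might infer that the planned analysis will overstate the child effect. The documents do not support that: they show that the pooled score cannot separate the two explanations, not that a shift will occur or which way it will go.

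**The magnitude is assumed.** Correct. The shift, the correlation and the number per arm are not in the documents, so the percentages illustrate a mechanism and do not measure an error in the plan.

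**The professional is not a clean reference.** Correct. Social workers are unblinded by the protocol's own statement. A reader might infer that a child-care worker completing the TRF is blinded because that role is not listed. Absence from the list does not show this, and it would concern only some TRF forms.

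**Rater turnover.** Families "usually reside in the domestic violence shelter for a period of 6 weeks to 9 months", so a reader might infer that the professional rater has changed by the week-7 post-test. Six weeks is the lower end of that range, ambulatory care follows, and no section says that raters change or that turnover differs between arms. The point does not rest on it.

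**These are secondary outcomes, and an analysis plan may add sensitivity analyses.** The blind-coded parenting outcomes are indeed unaffected. The pooling, however, is fixed in the article, and nothing there points to a separation of informants.

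**Conclusion.** The point holds as a limit on interpretation. Both child outcomes are specified only as informant-pooled scores, one informant is the unblinded mother whose view of the child NIKA works to change, and nothing in the protocol separates the informants. A result on the composite therefore cannot by itself be read as a change in the child.

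Under the stated assumptions, a shift in the mother's rating alone carries into the composite as about 0.18 to 0.32 SD and yields a significant result favouring NIKA in about 18 to 47% of trials. A shift in the other direction would hide a benefit to a corresponding degree. The primary outcomes are not touched. This is a change the sponsor should make, not one on which the trial depends.

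**What to change.** In Outcomes {12} and the statistical methods:

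- Keep the composite as the secondary outcome for each construct, and define it from informant scores standardised at baseline.
- Beside it, pre-specify as supportive analyses the mother-rated and professional-rated effects (CATS by informant; CBCL and TRF separately), each with a confidence interval, and an informant-by-condition term.
- State how they will be read. An effect carried only by the mother's rating, or with clear heterogeneity between informants, is described as a change in mother-reported symptoms and not as established child improvement.
- Do not accept mere agreement in sign from the professional as confirmation. Step 5 shows that it would let most false findings through. Judge the professional's estimate by its size and interval.
- Say in the limitations that the professional's rating is not blinded either, so separating the informants reveals a discrepancy but does not provide a blinded outcome.

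The cost is a few extra models on data already being collected. Each single-informant estimate is less precise than the composite, and the interaction test has limited power. Because the added estimates are supportive, they do not add to the number of confirmatory tests.
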